## Abstract

**Background:**

Atrial fibrillation (AF) has been recognised as an important independent risk factor for thromboembolic disease, particularly stroke for which it provides a five-fold increase in risk. This study aimed to determine the baseline prevalence and the incidence of AF based on a variety of screening strategies and in doing so to evaluate the incremental cost-effectiveness of different screening strategies, including targeted or whole population screening, compared with routine clinical practice, for detection of AF in people aged 65 and over. The value of clinical assessment and echocardiography as additional methods of risk stratification for thromboembolic disease in patients with AF were also evaluated.

**Methods:**

The study design was a multi-centre randomised controlled trial with a study population of patients aged 65 and over from 50 General Practices in the West Midlands. These purposefully selected general practices were randomly allocated to 25 intervention practices and 25 control practices. GPs and practice nurses within the intervention practices received education on the importance of AF detection and ECG interpretation. Patients in the intervention practices were randomly allocated to systematic (n = 5000) or opportunistic screening (n = 5000). Prospective identification of pre-existing risk factors for AF within the screened population enabled comparison between high risk targeted screening and total population screening. AF detection rates in systematically screened and opportunistically screened populations in the intervention practices were compared to AF detection rate in 5,000 patients in the control practices.

## Background

Atrial fibrillation (AF) has been recognised as an important independent risk factor for thromboembolic disease, particularly stroke with which it is associated with a five fold increase in risk [1]. There are few data on the prevalence of AF in the United Kingdom. Local data derived from the Echocardiographic Heart of England Screening (ECHOES) study suggested a prevalence of AF in people over the age of 65 of 3.8% (95% CI: 2.5–5.1) [2]. A review of four large community based studies of AF suggested that the overall community prevalence in the United States is 0.89% [3]. In these studies, the prevalence increased sharply with age: 2.3% of people aged 40 or over; 5.9% of people aged over 65 (higher than the local estimate), and 10% of those over 80. The vast majority (84%) of people with AF are over the age of 65. AF is a particularly important risk factor for stroke in the elderly – while 15% of all strokes are associated with the arrhythmia, it is associated with 36% of strokes in people over the age of 80. The incidence of new cases of AF in people over the age of 65 is of the order of 1% per annum [4].

Screening for AF in the elderly fulfils many of the Wilson-Jungner criteria for a screening programme [5]. It is a common and important condition which can be diagnosed by means of a simple test, and the risk of serious sequelae such as stroke can be dramatically reduced by treatment.

One UK study has compared systematic nurse-led screening with prompted opportunistic case finding for AF in primary care [6]. This small scale study (four practices, n = 3001) demonstrated that systematic nurse-led screening detected more cases than opportunistic case finding, however most of those cases detected were already diagnosed. Two further single practice based studies have investigated the role of practice nurses in the screening process [7], and whole population screening [8]. 5% of total NHS expenditure can be attributed to stroke, and there would be expected to be about 1,000 new cases of stroke per annum in a typical health authority of a half million population. Therefore, any programme that might lead to an important reduction in stroke incidence needs serious consideration, both because of the potential for health gain, and the potential for reduced overall NHS expenditure. Screening for AF might be one such programme since, in population terms, AF is an important risk factor for stroke and anticoagulation provides a highly effective treatment to reduce this risk. A meta-analysis of randomised controlled trials has shown a 68% relative risk reduction in patients' with AF receiving oral anticoagulation [9]. It has been estimated that optimal treatment of AF in the population might reduce the overall incidence of stroke by 10%. However, before implementing screening programmes, unresolved questions over how the screening should be conducted must be answered.

### The appropriate screening strategy to be employed

#### Opportunistic screening

The simplest strategy was *opportunistic case finding*, where a health care professional took the opportunity to feel a patient's pulse during a consultation. If the pulse is irregular, they might make a clinical diagnosis of AF, or request/perform an electrocardiogram (ECG) as a confirmatory test. However, opportunistic case finding is likely to miss a significant proportion of people who would otherwise have benefited from treatment. For example, detection of hypertension in general practice was traditionally detected in an opportunistic way until the introduction of health checks with the 1990 GP contract. The Health Survey for England shows that in 1991, 42% of the population over the age of 75 had hypertension for which they were not taking any medication [10]. This figure had fallen to 31% by 1994, after the GP contract had taken effect.

#### Targeted screening

One possible approach was to screen patients who are at higher risk of AF – a *targeted screening programme*. Cardiac failure, hypertension and rheumatic heart disease are important precursors of AF [7]. AF is more common in people with a history of myocardial infarction, angina, diabetes mellitus, hyperthyroidism, stroke or transient ischaemic attack (than in people without these conditions) [11]. Most general practices were computerised, and some have disease registers. A targeted screening programme could exploit these to identify such high risk patients, either through disease registers, or through prescribing information on the computerised records.

#### Whole population screening

Another approach was to screen everyone 65 and over (65+) for AF – a *whole population screening programme*.

A modelling exercise using decision analysis to inform on the methodology for this study indicated that there were not sufficient primary data available to recommend which of these (targeted or whole population) would be the optimum policy

#### The most appropriate screening test for AF

12-lead ECG is recognised as the gold standard test, but this test is time consuming (taking at least 15 minutes to perform in an outpatient setting). Therefore, it is important to consider simpler tests. This study assessed simpler methods compared to the gold standard, both in terms of accuracy, time taken and patient acceptability. These include taking the pulse, and simpler ECGs.

#### Interpreting the ECG

Cardiologists offer the most accurate readings of ECGs, but can satisfactory interpretations be obtained by the GP, the practice nurse, or computerised diagnostic software? This study assessed the accuracy of these different approaches to interpreting the ECG.

#### The value of echocardiography

The main treatment options to reduce risk of stroke in patients' with AF are currently warfarin or aspirin. Aspirin is much less effective than warfarin – it achieves a barely significant 21% reduction in stroke risk [9]. However, it is safer to use, since it confers a lower risk of serious haemorrhage. Therefore, in practice, the clinical decision as to which treatment to use depends upon the balance of risks and benefits for the individual patient. Thromboembolic risk is currently determined primarily on clinical criteria. Data from the SPAF study [12] suggested that echocardiography (Echo) may inform on risk stratification, assisting in therapeutic decision making. The role of routine Echo for patients with AF identified in the community remains to be proven. Data also needs to be quantified regarding the cost effectiveness of Echo versus clinical impression alone. Studies have suggested that the clinical utility in people aged over 74 is poor [13,14]. Therefore this study focused on patients aged 65–74. Once somebody has been identified as having AF, should they also receive an echocardiogram to assess their risk of stroke, or is clinical assessment of risk adequate?

#### Optimum strategy

This study, by providing answers to these questions, allowed the optimum strategy for introducing a screening programme for AF in the over 65s to be determined. However, before a decision is made as to whether to institute a screening programme, not only must the question of the best strategy be considered, but also, the question of whether any screening programme at all should be introduced. This study provided data to assist in answering this fundamental question by providing:

i) An accurate estimate of the community prevalence and incidence of AF in over 65s;

ii) An assessment of the health economic implications of screening for AF;

iii) An assessment of the service provision implications of implementing such a programme;

iv) An assessment of the impact on patient quality of life and anxiety after various screening methodologies.

#### Health economics of screening

Although the cost effectiveness of different approaches to screening is often put in terms of the average cost per case detected, such an approach ignores the sensitivity and specificity of the screening test. This is because average cost per case detected focuses entirely on true positives, paying no attention to false positives, false negatives and true negatives. False positives and false negatives impose costs on patients and health services which would be neglected if the focus was confined to true positives [15]. An undue emphasis on the average cost per case detected could justify opportunistic screening of a small number of high risk patients who present, with no consideration of the number of cases missed.

This study compared the incremental cost per case detected for different methods of AF screening. This refers not to the average cost but rather approximates the incremental cost per case detected in moving from one of the screening options to another. Use of incremental cost per case detected by option shows how the cost per additional case detected is likely to increase as the intensity of screening increases. This method has been used to deal with similar uncertainties about the cost effectiveness of screening for other diseases, including breast and colorectal cancer and has been recommended by the US guidelines [16].

### Objectives

#### Primary objective

• To determine baseline prevalence and the incidence of AF based on a variety of screening strategies and in doing so to evaluate the incremental cost-effectiveness, in terms of cost per case identified, of the different screening strategies (targeted or whole population screening) compared with routine clinical practice for detection of AF in people aged 65 and over.

#### Secondary objectives

• To evaluate the relative cost-effectiveness of screening methods for AF diagnosis, comparing 12 lead ECG (gold standard) with pulse taking, lead II rhythm strip from standard ECG limb leads alone and single lead thoracic placement ECG.

• To evaluate the most cost-effective method of test interpretation, comparing cardiologist (gold standard), with GP, practice nurse, or computerised diagnostic software.

• To assess the differing combinations of screening strategies and procedures in terms of patient acceptability and impact on patient quality of life, including any psychological effects of screening.

• To determine the community prevalence of AF in people 65+.

• To evaluate the value of clinical assessment and echocardiography as additional methods of risk stratification for thromboembolic disease in patients with AF.

• To evaluate the service provision implications should screening for AF become a national programme, and identify the optimum screening algorithm for identification of patients with AF.

### Outcome measures

#### Primary outcome

• The incidence of AF according to a variety of screening strategies

• The associated costs providing an incremental cost per case detected. The cost data was collected from an NHS and patient perspective. It has focused on resources required to establish screening, time taken to complete screening and the cost of the equipment.

#### Secondary outcomes

• Cost effectiveness of 4 different methods of screening for AF. The cost data focused on the difference in the cost of the equipment and the time taken for each of the different methods of screening to be completed. This was from both an NHS and patient perspective.

• Cost effectiveness of 4 different methods of ECG interpretation. The cost data focused on the difference in the cost of the grade of staff interpreting the ECG and the accuracy of their interpretation.

• Overall community prevalence and incidence of AF

• Patient acceptability to AF screening was measured using an adapted version of the screening specific questionnaire used in the Colorectal Screening Programme [18]. Patient uptake of screening was also monitored. The impact on quality of life was assessed using EQ-5D [24,25]. Patient anxiety was measured using the Spielberger 6 item Anxiety Questionnaire [17].

• Modelling techniques were used to identify the implications of AF screening on health service provision nationally. This included the effect on echocardiography and anti-coagulation clinic provision.

## Methods

This was a multi-centre randomised controlled trial. The study schema is shown in figure 1.

**Figure 1 F1:**
[figure not shown]
Study schema for the multi-centre randomised controlled trial.

50 computerised general practices within the West Midlands were recruited through MidReC (Midlands Research Practices Consortium). This was undertaken by writing to all practices in the West Midlands and surrounding counties explaining the study and asking whether they were interested in participating. Practices showing an interest were given further information about the study and invited to attend an investigators meeting. Following the investigator meetings sixty practices interested in participating in the project were randomised (stratified based on Townsend score and practice list size): 25 as intervention, 25 as control practices with 10 reserve practices.

A computerised list of all patients aged 65+ was obtained from each practice, and from this a random sample of 10,000 patients from the intervention practices (representing approximately ^1^/_3_^rd ^of the total population of patients 65+ in this group), and 5000 from the control practices (representing approx. ^1^/_6_^th ^of the total population of patients 65+ in this group) were identified.

Patients from intervention practices were randomised, by patient, to opportunistic or systematic groups. All patients within the systematic screening arm, including those with a history of AF, were invited by post to attend a screening clinic.

For patients in the opportunistic arm, their notes were flagged within the practice to encourage practice staff to undertake pulse recording. Patients with an irregular pulse were invited to attend a screening clinic. Once this process had been undertaken, the flag was removed from the notes and returned to the research team.

The screening clinic was run by practice nurses. Patients gave informed consent. Data collected was baseline information, past medical history (including any previous diagnosis of AF), radial pulse and a 12 lead ECG. The 12 lead ECG was performed using an electronic ECG machine which allowed print-out of single lead thoracic placement ECG and a rhythm strip of lead 2 using limb leads from standard ECG.

All 12 lead ECGs were sent to two cardiologists for reporting ([name]). Where there was disagreement over the diagnosis a third cardiologist was used to decide. The cardiologists were asked to state whether the ECG showed AF or not, and to state whether there were any other significant abnormalities. Patients were informed of the result within two weeks. Patients with normal ECGs were informed of this, patients with any abnormality were asked to make an appointment with their GP. At the GP appointment patients with AF aged 65 – 74 were offered echocardiography. GPs were asked to make a clinical decision as to thromboprophylaxis both before and after the echocardiogram. Patients with other ECG abnormalities were managed as clinically indicated.

At the end of the screening process, GPs and Practice Nurses from both intervention practices (who had received education on ECG interpretation) and control practices (who had received no education) were sent ECGs to interpret for the presence or absence of AF. All ECGs recorded within the study were printed off as either 12 lead, single lead thoracic placement or limb lead recordings. Allocation to ECG type was random and resulted in three equal ECG groups. In order for each interpreter to read all three types of ECG, batches of ECGs were collated with the same numbers of each type of ECG. Allocation to a batch was also random. In total, there were 25 batches of ECGs to match the number of practices in each arm. The GP and Practice Nurse from the same practice read the same batch of ECGs and each batch was read by one control practice and one intervention practice. Therefore each ECG was read by two GPs and two Practice Nurses. All ECGs were anonymised, and practices did not receive any ECGs from their own practice. The interpreters were given a sheet to fill in to indicate for each ECG the presence or absence of AF. All ECGs (as 12 lead) were also analysed by the specific software package accompanying the electronic ECG and results recorded.

Patient acceptability and quality of life for different screening strategies were established using EuroQol (EQ-5D) combined together with the Speilberger 6-item Anxiety Questionnaire. EQ-5D allowed the measurement of broad aspects of quality of life. The shortened Speilberger anxiety questionnaire also has proven validity and is more specific to anxiety than is the SF-12 [17]. An adapted version of the screening-specific tool used in the Colorectal Screening Programme [18] was used to assess the acceptability of the screening process.

A random sample of 750 patients (375 screened patients and 375 opportunistically screened patients) were sent postal versions of the psychological instruments (EQ-5D and Spielberger) on entry to the study (i.e. before the intervention group has received their invitation to attend for screening). One reminder was sent a month later to non-responders. The same questionnaires were sent to the same groups plus those patients who had screened postive at the end of the screening period, approximately 17 months later. This allowed a non-randomised comparison between the effects on quality of life and anxiety in screen positive and screen negative patients.

In addition, all patients who were screened were asked to complete the acceptability and Spielberger questionnaire immediately after screening. The patient acceptability questionnaire was also administered to all patients who proceeded for echo.

The value of clinical assessment and echocardiography in risk stratification were determined in patients aged 65–74. This compared GP assessment based on the Birmingham guidelines for thromboprophylaxis in AF with any changes in recommendations for treatment once echocardiography results were available to the GP.

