*f) To detect a relative risk (RR) of 2 (1% detection rate difference) between total population and high risk screening (A3 vs A2).*It was assumed that 40% of the study population fall into the high risk group, and the prevalence of undetected AF is 3%. This meant that 1,434 patients would be needed in each of the two risk groups to detect a two fold difference in risk (i.e. RR of AF in high risk as compared to low risk group is 2). This RR of 2 equates to an increase in AF detection rate from 3% in the total population arm to 4% in the high risk arm. Since there was a 40:60 split in the two risk groups unequal sample size calculations only require a minimum of 1,200 patients in the high risk group and 1,800 in the moderate/low risk group. This was achievable with a screening arm of 5,000 patients, as there would actually be 1,320 in the high risk group and 1,980 in the moderate risk group if a 66% screening acceptance rate was assumed.

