#### Data on consequences

The use of EQ-5D allows the measurement of broad aspects of quality of life. EQ-5D allows changes in health status to be measured but also valued, using the University of York Measurement & Valuation of Health general population survey tariff [27].

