#### Screening clinics

All patients in the systematic screening arm and those found to have an irregular pulse in the opportunistic screening arm of the study were invited to attend an ECG screening clinic. At the clinic the practice nurse explained the aims of the study and answered any questions about the study. Written informed consent to participation in the study was obtained from the patient. The nurse then recorded baseline information on age, sex, present smoking and alcohol status and past medical history, including previous diagnosis of AF, and any treatment the patient may be receiving for AF. Radial pulse rate, and whether regular or irregular, was noted. A 12 lead ECG, the gold standard by which other traces were compared, was then recorded using the Biolog machine, which was also able to produce a trace corresponding to the single lead thoracic placement and a rhythm strip of lead II. Finally, the patient was asked to complete an acceptability questionnaire.

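### For EQ-5D, the screen positive v screen negative contrast compares 17-month levels, not effects: only about 7.5% of positives are sent the form before their result

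*Protocol article*

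**What the plan says.** The schedule is in the Methods of the protocol article, in the paragraphs on acceptability and quality of life that follow Figure 1.

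- Before invitations: "A random sample of 750 patients (375 screened patients and 375 opportunistically screened patients) were sent postal versions of the psychological instruments". The instruments are EQ-5D and Spielberger.
- About 17 months later: "The same questionnaires were sent to the same groups plus those patients who had screened postive at the end of the screening period".
- At the clinic: "all patients who were screened were asked to complete the acceptability and Spielberger questionnaire immediately after screening". The section on screening clinics mentions only the acceptability form: "Finally, the patient was asked to complete an acceptability questionnaire". Neither place mentions EQ-5D.
- What this is said to permit: "This allowed a non-randomised comparison between the effects on quality of life and anxiety in screen positive and screen negative patients".

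The section on targeted screening states that "AF is more common in people with a history of myocardial infarction, angina, diabetes mellitus, hyperthyroidism, stroke or transient ischaemic attack", and the Background says that AF rises sharply with age. Patients with a history of AF are invited in the systematic arm, and the sample size section expects half of all AF to be known already. Results reach patients within two weeks of the ECG.

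**The concern.** A comparison of effects between groups that were not randomised needs to know where each group started. For EQ-5D, nearly all positives contribute one score, taken long after the result. All negatives come from the 750 who were also sent the form before screening. The article itself gives reasons to expect positives to be older and sicker at the outset.

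At stake is the reading of a lower EQ-5D in positives at 17 months. It could be taken as harm from being told of AF when it reflects illness present before screening. Because this is a matter of what was collected, no later analysis plan can supply the missing starting scores. Adjustment for recorded history can only stand in for them.

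**Working it through.** **The plan's own figures.** With n per group = 2 × variance × (1.960 + 1.282)² / difference²:

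| Measure | Variance | Difference | Computed | Stated |
|---|---|---|---|---|
| Spielberger | 188.8 | 4 | 248.0 | 249 |
| EQ-5D VAS | 365 | 6 | 213.1 | 213 |
| Utility, first source | 0.066 | 0.1 | 138.7 | 139 |
| Utility, second source | 576 | 7 | 247.0 | 247 |

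These reproduce. They size groups for comparing arms; the article sets no target difference for positive v negative.

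**Share of positives with a starting EQ-5D.** The sample is random and drawn before invitation, so it cannot depend on attendance or result. The expected share is 375 / 5,000 = 7.5% per arm, leaving 92.5% without, whatever the uptake or prevalence. Non-response raises this: at an assumed 80% response, 1 − 0.075 × 0.8 = 94%. By the hypergeometric distribution, the realised share without a form would be about 89 to 96% with 198 positives.

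**Counts in the systematic arm** (66% uptake, 6% AF and half known, all from the sample size section):

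- All positives: 5,000 × 0.66 × 0.06 = 198; with a starting EQ-5D: 375 × 0.66 × 0.06 = 14.9.
- New AF only: 99; with a starting EQ-5D: 7.4.
- Negatives in the sample: 375 × 0.66 × 0.94 = 233. If the opportunistic arm is assumed to have the same uptake and AF rate, both arms give 465.

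**How far case mix alone could mislead.** The sample size section takes 40% of patients as high risk, undetected AF of 3%, and "RR of AF in high risk as compared to low risk group is 2".

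- AF in the low risk group: 0.03 / (0.6 + 0.4 × 2) = 0.0214; in the high risk group: 0.0429.
- High risk share among new AF: 0.4 × 0.0429 / 0.03 = 0.571.
- High risk share among the rest: 0.4 × 0.9571 / 0.97 = 0.395.
- Gap: 0.177.

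Let high risk patients score D lower in utility. D is not in the document and is assumed to be 0 to 0.2. The unadjusted bias is b = 0.177 × D. With SD = √0.066 = 0.257 and 99 new cases, the standard error is 0.257 × √(1/99 + 1/465) = 0.0284 against both arms' negatives, and 0.0308 against the 233. The chance of p < 0.05 with no true effect is:

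| D | b | v 465 negatives | v 233 negatives |
|---|---|---|---|
| 0 | 0 | 5% | 5% |
| 0.1 | 0.018 | about 9% | about 9% |
| 0.2 | 0.035 | 24% | 21% |

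Adjusting for the recorded risk group would remove this modelled part among systematic patients. Age within risk group, severity of illness and other differences in starting health are not modelled and would remain.

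**Anxiety.** All screened patients complete a Spielberger form straight after screening. The ECGs then go to cardiologists, and the result follows within two weeks. A value from before the result therefore exists.

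**The case against.** The best defence is that the article already calls the contrast non-randomised, and that it is a side comparison. The secondary objective concerns screening strategies and procedures, and the analysis section tests differences between the intervention strategies. That randomised comparison is untouched. This stands, and it limits the weight of the point. It does not settle it: the label concedes that the groups may differ, but it neither supplies a starting EQ-5D nor makes a 17-month level an effect.

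Three stronger readings are tempting, and the document does not support them.

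- *A false positive rate as high as 37%.* That arises if all 198 positives are used at D = 0.2, unadjusted, against 465 negatives. But the relative risk of 2 is set for undetected AF, so it belongs with the 99 new cases. The article names no such unadjusted test, and its analysis section foresees possible adjustment if demographic differences appear.
- *A shortfall against a planned 0.1 utility.* That difference sizes the arms. No one proposes analysing only the 15 positives with a starting value.
- *A broken promise to measure change.* The economic section's "EQ-5D allows changes in health status to be measured but also valued" describes the instrument. It is not a claim about this contrast.

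It is also fair to say that collection appears to be over, since the Discussion reports that a draft report has been submitted. The practical remedy is then analysis and wording.

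**Conclusion.** The point holds for EQ-5D in the positive v negative contrast and no further. An expected 92.5% of positives have no EQ-5D from before their result. This rests only on the stated sampling fraction and on no clinic EQ-5D being described. The contrast compares levels at 17 months between groups expected to differ at the outset.

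The size of the resulting bias cannot be determined from the document. The 0 to 0.035 utility and 5 to 24% false positives are illustrative. They rest on an assumed D of 0 to 0.2, on 99 new cases and on no adjustment; at D = 0 this source gives no bias. A reader might infer that the anxiety findings or the quality of life objective as a whole are compromised. They are not: anxiety has a value from before the result, and the randomised comparison of strategies serves the objective.

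**What to change.** **If collection can still change.** Give EQ-5D at the clinic, before the ECG, to systematic-arm attenders. Compare 17-month scores, adjusted for that value, between newly found AF and no AF, with confidence intervals. Report previously known AF separately, since for those patients the result is not news; the clinic already records it.

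The cost is one short form for about 5,000 × 0.66 = 3,300 attenders, at a visit where questionnaires are already given. With 99 new cases v 233 negatives and an assumed correlation of 0.3 to 0.7 between the two scores, power for a 0.1 utility difference is 93 to 99% (81 to 97% at an assumed 70% response). For 4 Spielberger points, adjusted in the same way, it is 72 to 93% (57 to 81%). The drawback is that a clinic value follows the invitation, so it isolates the result and not the invitation. Confounding other than through the starting score remains.

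**If collection is over.** Restrict the contrast to systematic attenders and separate known from new AF. Adjust anxiety for the Spielberger taken straight after screening. Adjust EQ-5D for age, sex, risk group and recorded history, and report it as a difference at 17 months, not an effect of the result. This costs only analysis time and wording.
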